
### Intervention

All patients who underwent imaging or pathological evaluation and, if they met the inclusion criteria, were enrolled and provided informed consent. Enrolled patients received a combined treatment regimen of XELOX chemotherapy, sintilimab immunotherapy, and HBOT. The XELOX regimen consisted of oxaliplatin 130 mg/m² administered by intravenous infusion on Day 1 and capecitabine 1000 mg/m² taken orally twice daily on Days 1–14 of each 3-week cycle. Sintilimab was given as a 200 mg intravenous infusion on Day 1 of each cycle. On Day 1 of each cycle, patients first received the sintilimab infusion followed by the oxaliplatin infusion, and immediately after completing these infusions, they underwent a 1-hour HBOT session at 2 ATA later the same day. Efficacy was assessed every two cycles. After six cycles, patients with tumor progression exited the study to receive further treatment, whereas those without progression continued maintenance therapy with capecitabine plus sintilimab until disease progression, intolerable toxicity, initiation of a new antitumor treatment, withdrawal of consent, loss to follow-up, death, or any other investigator-determined reason for discontinuation, whichever came first. If any component of the treatment was discontinued for any reason, the remaining components were continued as appropriate. If a participant becomes resectable during therapy and undergoes surgery per MDT decision, study treatments may be held or discontinued to allow surgery. The participant remains on study and transitions to the follow-up phase, with continued assessments of safety and survival endpoints. **Figure 2** illustrates the study design schematic.

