### Endpoints

The primary goal of Phase Ib is to assess the safety and tolerability of the XELOX regimen combined with sintilimab and HBOT in treating advanced or metastatic GC/GEJ adenocarcinoma and to determine the optimal HBOT protocol for Phase II.

The primary endpoint of Phase II is the objective response rate (ORR). The secondary endpoints include PFS, DCR, two-year DFS (for patients converted to resectable disease and achieving R0 resection), two-year OS, and quality of life and safety profiles. Adverse events (AEs) will be recorded and evaluated according to the National Cancer Institute Common Terminology Criteria for Adverse Events (NCI CTCAE, version 5.0). Severe adverse events (SAEs) are defined as death, hospitalization or prolonged hospitalization, permanent or severe disability, congenital anomalies, or other significant clinical sequelae.

Exploratory biomarkers will be collected at prespecified timepoints from tumor tissue (CD8^+^ T−cell density; HIF−1α and CAIX), blood (CD4%, CD8%, and the CD4:CD8 ratio), and fecal samples (Shannon diversity index); analyses are descriptive and hypothesis−generating, as detailed in **Supplementary File 1**. Samples will be processed and stored in a secured biobank following standard operating procedures. Any future research using stored samples will require separate ethical approval.

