**Figure 2 f2:**
[figure not shown]
Schematic overview of the phase Ib/II trial design. Patients with pathologically confirmed, unresectable, HER2−negative advanced or metastatic gastric or gastroesophageal junction adenocarcinoma receive first−line therapy. Phase Ib uses a 3 + 3 design to evaluate HBOT schedules and select the recommended Phase II dose. Phase II enrolls 48 patients who receive six 21−day cycles of XELOX plus sintilimab and HBOT at the selected dose, with imaging every two cycles. Patients without progression after six cycles transition to maintenance with capecitabine plus sintilimab, and HBOT is not continued. Patients who progress at any time discontinue protocol therapy and proceed to subsequent treatment.

Treatment adherence will be ensured by maintaining drug accountability records for capecitabine and infusion records for oxaliplatin and sintilimab. HBOT attendance will be logged at each session. Study staff will monitor adherence at every visit, and any deviations from the protocol will be recorded and evaluated. Supportive care measures, such as antiemetics, antibiotics, and analgesics, will be permitted as clinically indicated. The use of corticosteroids is allowed only at physiological doses (≤10 mg/day of prednisone or equivalent). Concomitant anticancer therapies, including radiotherapy, targeted therapy, and additional immunotherapies, are prohibited during the trial. Participants will be recruited from outpatient and inpatient services at West China Hospital through clinician referrals, review of clinic schedules, and study advertisements. Regular reminders via telephone or electronic messaging will promote participant retention. For participants who discontinue the intervention prematurely, available outcome data will be collected up to the point of withdrawal for analysis.

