Secondary efficacy endpoints will be analyzed and reported descriptively. PFS is defined as the time from treatment initiation until radiologic disease progression or death. It will be estimated using the Kaplan-Meier method; the median PFS and its two-sided 95% confidence interval will be reported. Patients who are alive without progression at the time of analysis will be censored at the date of their last disease assessment. DCR is the percentage of patients achieving CR or PR or sustained stable disease for at least 6 weeks. DCR will be reported with a two-sided 95% exact confidence interval calculated by the Clopper-Pearson method. For the subset of patients who undergo curative-intent surgery (R0 resection) after successful therapy, a 2-year DFS rate will be calculated. This rate will be defined as the proportion of those post-surgery patients who are alive and recurrence-free 24 months after surgery. Because this subset is expected to be small, the 2-year DFS will be presented as a descriptive metric without formal statistical comparison. OS is defined as the time from treatment initiation until death from any cause. The 24-month OS rate will be estimated using Kaplan-Meier methods, and if sufficient follow-up is available, the median OS and its 95% confidence interval will also be reported. If the median OS is not reached by the analysis time, the survival rate at the last follow-up time point will be provided instead. Patients who are alive at the time of analysis (or last known follow-up) will be censored on that date for OS and DFS analyses. Patient-reported quality of life outcomes will be summarized at baseline and at specified time points during treatment. Changes from baseline in QoL scores may be explored with paired statistical tests, depending on data distribution, as an exploratory analysis.

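### The article has progressing patients leave the study, yet two-year OS counts deaths after progression; followed as written, 24-month OS would be biased upward

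*Protocol article*

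**What the plan says.** **Endpoint.** The Endpoints section lists "two-year OS, and quality of life and safety profiles" among the Phase II secondary endpoints. Under Efficacy endpoints, "OS is defined as the time from treatment initiation until death from any cause", and "The 24-month OS rate will be estimated using Kaplan-Meier methods". Deaths after progression therefore count.

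**Patients who progress.** The Intervention section says: "After six cycles, patients with tumor progression exited the study to receive further treatment". The Figure 2 caption says: "Patients who progress at any time discontinue protocol therapy and proceed to subsequent treatment".

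**Patients who stop early.** The adherence paragraph after that caption says: "For participants who discontinue the intervention prematurely, available outcome data will be collected up to the point of withdrawal for analysis".

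**Patients who have surgery.** The Intervention section says: "The participant remains on study and transitions to the follow-up phase, with continued assessments of safety and survival endpoints". The Discussion likewise promises prospective follow-up of surgical patients.

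**Censoring of OS.** Efficacy endpoints censors living patients at the analysis date or the last contact. Missing data names OS together with PFS and DFS, and censors all three at the latest adequate disease assessment. Under the Figure 1 caption, imaging runs every two cycles until progression.

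**The concern.** The endpoint needs vital status to 24 months in every patient, and most deaths in this disease can be expected to follow progression. The conduct text takes patients with progression out of the study, and no passage provides survival follow-up for them. This goes beyond detail lost in condensing. The same paragraph sets leaving the study against remaining on it, and gives survival assessment only to the second group.

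Censoring at progression is informative, because a patient who has just progressed has a higher risk of death than one who has not. Kaplan-Meier assumes that censored patients share the later risk of those still observed, so the curve would sit too high. Vital status that is not collected while the trial runs may be hard to recover later.

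**Working it through.** **Plan's own figure.** The article states no OS or PFS rate and no OS precision target, so there is no OS figure to reproduce. Its only sample-size figure concerns ORR. The normal approximation [(1.2816·√(0.58·0.42) + 0.8416·√(0.73·0.27))/0.15]² gives 44.99, so 45, and 45/0.95 gives 48 after rounding up. OS does not enter that calculation.

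**Side by side.**
- *Status at progression:* out of the study (Intervention), or off protocol therapy only (Figure 2 caption).
- *Censoring at last contact:* for a patient who has left, this is about the exit date.
- *Censoring at the latest tumour assessment:* imaging ends at progression, so this date is also at or near progression.

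If exit is taken literally, both censoring rules give nearly the same date. If deaths after exit were collected after all, the tumour-assessment rule would discard survivors' time alive after their last scan while counting the deaths. That is a separate distortion, in the downward direction, so this rule needs correcting in either case.

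**Size (all rates are assumptions).** Time to progression or death is exponential with rate λ = ln2/(median PFS). A share q of these first events are deaths. Post-progression survival is exponential with rate μ = ln2/(its median). At t = 24 months:
- True OS = e^(−λt) + (1−q)·λ/(λ−μ)·(e^(−μt) − e^(−λt)).
- Kaplan-Meier OS if every progression is censored = e^(−qλt).

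Example with medians 7 and 8 months and q = 0.15: λt = 2.3765 and e^(−λt) = 0.0929; e^(−μt) = 0.125; λ/(λ−μ) = 8.
- True OS = 0.0929 + 0.85·8·(0.125 − 0.0929) = 0.0929 + 0.218 = 0.311.
- Censored at progression = e^(−0.15·2.3765) = 0.700.

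Narrow reading: only patients who progress within six cycles (18 weeks, 4.14 months) leave, and everyone else is followed to death. This was simulated.

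Simulation results (200,000 patients in the first five rows, 400,000 in the rest; the first two OS columns agree with the formulas to within about 0.2 points):

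| Median PFS | Median post-progression | q | True 24-month OS | Every progression censored | Only progression within six cycles censored |
|---|---|---|---|---|---|
| 7 | 6 | 10% | 25.6% | 78.7% | 33.5% |
| 7 | 8 | 10% | 32.5% | 78.9% | 40.3% |
| 8 | 8 | 10% | 35.9% | 81.2% | 44.0% |
| 8 | 10 | 10% | 41.5% | 81.4% | 49.2% |
| 10 | 10 | 10% | 47.4% | 84.8% | 55.0% |
| 7 | 8 | 15% | 31.1% | 69.9% | not run |
| 7 | 8 | 25% | 28.7% | 55.3% | not run |
| 8 | 10 | 15% | 39.9% | 73.2% | not run |
| 7 | 12 | 15% | 41.3% | 70.2% | not run |

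- Every progression censored: bias from 55.3 − 28.7 = 26.6 points to 78.7 − 25.6 = 53.1 points. In the first five rows only 12%-15% of deaths by 24 months are observed.
- Only early progression censored (23%-30% of patients): bias from 55.0 − 47.4 = 7.6 points to 44.0 − 35.9 = 8.1 points.

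**The case against.** The strongest reply is that leaving the study was meant as leaving treatment. The exit clause is tied to the period after six cycles, the Figure 2 caption speaks only of protocol therapy, and the Intervention section refers to a follow-up phase as something that already exists. The full protocol, version 1.3, may set out survival follow-up. That may well be the intention, and it is why the larger bias cannot be taken as the expected size. It does not remove the point: the article states study exit, and its passages disagree.

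A reader might also infer more than the documents support:

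- *That two-year OS cannot be observed at all.* Deaths before progression and deaths of resected patients remain observable. An estimate exists, but it is biased.
- *That outcome collection ends whenever treatment stops early.* The adherence paragraph says "available outcome data will be collected up to the point of withdrawal for analysis". Elsewhere the article lists withdrawal of consent as one separate reason for stopping and pairs withdrawal with loss to follow-up, so consent may be what is meant.
- *That ORR and PFS suffer from lost scans.* The Figure 1 caption schedules imaging until progression without making it depend on treatment, and exit at progression comes after the PFS event.
- *That an inflated OS would be set against historical results.* Efficacy endpoints plans that comparison for ORR, and none is planned for OS.
- *That a true 31% reported as 70% is the size of the problem.* The arithmetic is right, but it rests on assumed rates and on the broadest reading of the exit clause.

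**Conclusion.** The point holds at moderate severity. The article contradicts itself on whether progressors leave the study or only protocol therapy, gives two different OS censoring rules, and promises survival follow-up only to surgical patients. Followed as written, 24-month OS is biased upward, by about 8 points on the narrow reading and roughly 25-55 points on the broad one. The upward direction depends on deaths after exit going uncollected and on progression raising the risk of death. The sizes depend on exponential times and assumed medians, none of which comes from the documents. OS is a secondary, descriptive endpoint and no decision rule uses it. The primary endpoint, PFS and the sample size are not shown to be affected.

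**What to change.** 1. Reconcile the Intervention section with the Figure 2 caption by separating end of protocol treatment from end of study. No treatment rule needs to change for this.
2. State that all patients who progress or stop treatment early are followed for vital status to death or at least 24 months, unless they withdraw consent to follow-up.
3. In the adherence paragraph, make clear that withdrawal means withdrawal of consent.
4. Use one OS censoring rule, the date last known alive, and remove OS from the tumour-assessment rule under Missing data.

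Cost: revised wording, plus periodic telephone or record checks for about 57 patients (48 in Phase II and about nine in Phase Ib). The trial already uses telephone reminders. Recruitment is planned to run to about 31 December 2026, so the change can still take effect.

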**Figure 2 f2:**
[figure not shown]
Schematic overview of the phase Ib/II trial design. Patients with pathologically confirmed, unresectable, HER2−negative advanced or metastatic gastric or gastroesophageal junction adenocarcinoma receive first−line therapy. Phase Ib uses a 3 + 3 design to evaluate HBOT schedules and select the recommended Phase II dose. Phase II enrolls 48 patients who receive six 21−day cycles of XELOX plus sintilimab and HBOT at the selected dose, with imaging every two cycles. Patients without progression after six cycles transition to maintenance with capecitabine plus sintilimab, and HBOT is not continued. Patients who progress at any time discontinue protocol therapy and proceed to subsequent treatment.

Treatment adherence will be ensured by maintaining drug accountability records for capecitabine and infusion records for oxaliplatin and sintilimab. HBOT attendance will be logged at each session. Study staff will monitor adherence at every visit, and any deviations from the protocol will be recorded and evaluated. Supportive care measures, such as antiemetics, antibiotics, and analgesics, will be permitted as clinically indicated. The use of corticosteroids is allowed only at physiological doses (≤10 mg/day of prednisone or equivalent). Concomitant anticancer therapies, including radiotherapy, targeted therapy, and additional immunotherapies, are prohibited during the trial. Participants will be recruited from outpatient and inpatient services at West China Hospital through clinician referrals, review of clinic schedules, and study advertisements. Regular reminders via telephone or electronic messaging will promote participant retention. For participants who discontinue the intervention prematurely, available outcome data will be collected up to the point of withdrawal for analysis.

### Safety monitoring

Safety monitoring for all treatments in this study, including chemotherapy, immunotherapy, and HBOT, is conducted in accordance with CTCAE v5.0 criteria. In particular, for HBOT-related toxicity, predefined criteria for early treatment interruption or permanent discontinuation, as well as procedures for monitoring and managing severe adverse events, have been established. The plan also defines SAE identification, documentation, expedited reporting, and escalation pathways. Full procedures and dose−modification tables (including Chemotherapy, Immunotherapy, and HBOT) are provided in **Supplementary File 2**. Investigators will evaluate, document, and report all AEs in real time, follow patients to resolution/stability, and act according to protocol−defined thresholds.

### Statistical analysis

#### Analysis populations

Three analysis populations were defined for this study: the Intent-to-Treat (ITT) population, the Per-Protocol (PP) population, and the Safety population. The ITT population includes all patients who provided informed consent and received any amount of study treatment. In practice, this means patients who received at least one dose of the study therapy or underwent at least one HBOT session. The PP population consists of patients who met all key eligibility criteria, had no major protocol violations, completed at least two treatment cycles, and had evaluable data for the primary endpoint. The Safety population comprises all patients who initiated study treatment, meaning they received at least one dose of the study drug or at least one HBOT session.

Efficacy analyses will primarily use the ITT population, while the PP population will be analyzed in a sensitivity context to assess the impact of protocol deviations. All safety analyses will use the Safety population. In addition, patients from the Phase Ib portion of the trial who received the same HBOT regimen as selected for Phase II will be combined with the Phase II patients to form a pooled RP2D analysis set. This combined dataset will be used for supportive analyses of efficacy and safety endpoints. The pooled Phase Ib+II results will be presented alongside the Phase II–only results to provide additional context, but they will not serve as the primary basis for any efficacy conclusions and will not influence the primary analysis in the Phase II ITT population. Tables of results will clearly indicate whether each patient came from Phase Ib or Phase II.

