#### Efficacy endpoints

This is a single-arm exploratory trial; therefore, all efficacy results will be descriptive with no formal between-group comparisons. The primary efficacy endpoint for Phase II is the ORR, defined as the proportion of patients achieving a best overall response of CR or PR as determined by investigator assessment according to RECIST v1.1. The first tumor assessment is scheduled at approximately 6 weeks of therapy, which corresponds to the end of two treatment cycles. ORR will be reported along with a two-sided 95% exact confidence interval calculated using the Clopper–Pearson method. In the ITT analysis, patients with no post-baseline tumor assessments will be considered non-responders for the purpose of calculating ORR. The observed ORR will be compared qualitatively to historical outcomes from first-line therapy for advanced GC/GEJC; however, no formal hypothesis testing will be performed due to the single-arm study design.

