#### Sensitivity analyses and missing data

##### Sensitivity analyses

The robustness of the primary endpoint analysis will be examined through predefined sensitivity analyses. In addition to the main ORR analysis conducted on the ITT population, the ORR will also be calculated for the PP population to evaluate the impact of any protocol deviations on the primary outcome. Furthermore, as an exploratory sensitivity analysis concerning PD-L1 status, the effect of using an alternative PD-L1 expression cutoff will be assessed: specifically, outcomes will be examined using a CPS threshold of 5 (CPS ≥5 vs. <5), as was prespecified before the trial.

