##### Missing data

For the primary endpoint ORR in the ITT population, patients who have no post-baseline tumor assessments will be counted as non-responders. For time-to-event endpoints such as PFS, DFS, or OS, patients who have not experienced the event by the cutoff date will be censored at the time of their last adequate disease assessment. If scheduled visits or assessments are missed, all data collected up to the point of patient withdrawal or loss to follow-up will be included in the analysis, and no forward imputation of missing future observations will be performed. Missing data in patient-reported outcome measures, such as QoL questionnaires, will not be imputed; analyses will be based on available data only.

To address the potential impact of missing data, we may conduct additional exploratory analyses using methods that accommodate data missing at random. For example, a linear mixed-effects model for repeated measures could be employed to explore longitudinal trends in QoL scores despite some missing follow-up data. If more than 10% of patients have missing data for the primary endpoint, we will perform additional sensitivity analyses to ensure the robustness of our conclusions. These may include using multiple imputation techniques to estimate missing outcomes and conducting best-case and worst-case scenario analyses to gauge the potential range of impact due to the missing data.

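### The per-protocol ORR drops patients who fail before the first scan, so it mixes early treatment failure with the protocol deviations it is meant to measure

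*Protocol article*

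**What the plan says.** Under Analysis populations, the PP set requires key eligibility, no major protocol violations, and two further conditions: that the patient "completed at least two treatment cycles, and had evaluable data for the primary endpoint". The same section gives its purpose: "the PP population will be analyzed in a sensitivity context to assess the impact of protocol deviations". Sensitivity analyses repeats that purpose for the primary endpoint: "the ORR will also be calculated for the PP population to evaluate the impact of any protocol deviations on the primary outcome".

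The timing is under Efficacy endpoints: "The first tumor assessment is scheduled at approximately 6 weeks of therapy, which corresponds to the end of two treatment cycles". The Figure 2 legend adds: "Patients who progress at any time discontinue protocol therapy and proceed to subsequent treatment". Under Intervention, partial stops are treated differently: "If any component of the treatment was discontinued for any reason, the remaining components were continued as appropriate".

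The primary analysis handles unscanned patients explicitly: "In the ITT analysis, patients with no post-baseline tumor assessments will be considered non-responders for the purpose of calculating ORR". Further checks on missing response data are conditional: "If more than 10% of patients have missing data for the primary endpoint, we will perform additional sensitivity analyses".

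**The concern.** Two of the PP conditions depend on what happens after treatment starts, and both are settled at about the time of the first scan. Early death, progression before the scan, or a full stop for toxicity is an outcome of the regimen, not a departure from the protocol. The condition on major violations already covers departures. The two extra conditions add selection on outcome, so a difference between the ITT and PP ORR cannot be read as the effect of deviations, which is the only purpose the article gives it.

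The PP ORR is also the only re-estimate of the overall Phase II ORR that is certain to be produced as a sensitivity analysis. The CPS 5 analysis re-splits a subgroup display, the pooled Phase Ib and II set is labelled supportive, and the missing-data analyses need a trigger. In an open-label trial with investigator-assessed response and a qualitative comparison with history, a PP figure above the ITT figure could be taken as reassurance when it partly reflects the removal of failures.

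**Working it through.** **Who is removed.** Setting the sections side by side:

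| Event | ITT ORR | PP set as written |
|---|---|---|
| Death before the first scan | non-responder | excluded (fewer than two cycles, no response data) |
| Progression before the end of cycle 2 | non-responder | excluded (therapy stops, so two cycles are not completed) |
| Whole regimen stopped for toxicity before the end of cycle 2 | non-responder if never scanned; otherwise as assessed | excluded |
| Progression first seen at the scheduled 6-week scan | non-responder | not excluded by these conditions (two cycles are complete) |
| One component stopped, others continued | as assessed | need not be excluded; the article does not define completion of a cycle |

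**Inputs.** Phase II enrolment is 48, from the Methods section: 45/(1 − 0.05) = 47.4, rounded up to 48, which reproduces the article's figure. The design rates are 58% (historical) and 73% (target). The article gives no figure for the PP set and no early-failure rate, so k, the number removed by the two conditions, is an assumption.

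**Formula.** With x responders among 48 treated patients, and k patients removed of whom j are responders:

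ITT ORR = x/48; PP ORR = (x − j)/(48 − k).

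PP exceeds ITT exactly when j/k < x/48, that is, when those removed respond less often than the ITT set.

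**All removed patients are non-responders (j = 0), x = 28, ITT 58.3%:**

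- k = 2: 28/46 = 60.9% (+2.5 points)
- k = 4: 28/44 = 63.6% (+5.3 points)
- k = 5: 28/43 = 65.1% (+6.8 points)

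**The same with x = 35, ITT 72.9%:** k = 2 gives 35/46 = 76.1%; k = 5 gives 35/43 = 81.4%.

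**Some removed patients are responders, x = 28, k = 5:** j = 2 gives 26/43 = 60.5% (+2.1 points); j = 3 gives 25/43 = 58.1% (−0.2 points); j = 4 gives 24/43 = 55.8% (−2.5 points).

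**The 10% trigger.** 10% of 48 is 4.8, so at least five patients must lack primary-endpoint data. If four early failures are the only missing cases (4/48 = 8.3%), the trigger is not reached, although the PP shift is 5.3 points, about a third of the 15-point design difference (73 − 58).

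**Scale.** The 95% Clopper–Pearson interval for 28/48 is 43.2% to 72.4%. Each shift in the x = 28, j = 0 list leaves the PP estimate inside it.

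**The case against.** The strongest reply is that nothing important depends on the PP figure. The headline ORR is ITT, it already counts unscanned patients as non-responders, both figures will be reported, and no rule or test uses the PP result. That is correct, and it limits the severity.

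It can also be said that a minimum-exposure PP set answers a legitimate question about response among adequately treated, evaluable patients. It does, but the article does not give that as its purpose; it names protocol deviations twice.

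The size is also open to challenge. The nearest planning figure is 5% attrition, about two patients (0.05 × 48 = 2.4), which corresponds to a shift of about 2.5 points. ECOG 0–1 and predicted survival over three months limit early failures without excluding them. If more than 10% lack response data, the article commits to further analyses, and only the choice of method is optional. This helps with larger losses, but not below the trigger, and a worst case that scores missing scans as non-response repeats the ITT analysis.

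Three stronger readings are tempting and are not supported:

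- That the PP ORR can only exceed the ITT ORR. PP also excludes ineligible patients and major violators, who may be responders, and a patient who stops early could still have a response on a scan.
- That the PP result could carry an inactive regimen past the 58% benchmark. The historical comparison is qualitative, the sample-size paragraph calls itself non-confirmatory, and no conclusion is tied to PP.
- That all early progressions and toxicity stops are removed. Progression at the 6-week scan and single-component stops need not be.

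**Conclusion.** The point holds as a minor-to-moderate flaw in a descriptive sensitivity analysis. The two post-baseline conditions remove patients for outcomes rather than deviations, so the PP ORR does not isolate what the article says it measures. The direction is upward provided the patients removed by those conditions respond less often than the ITT set, which is likely for deaths and pre-scan progression but not guaranteed for toxicity stops. For an ITT ORR of 28/48, the shift is about 2.5 to 6.8 points if two to five patients are removed and none is a responder. Those counts are illustrative; the article fixes no rate. The primary ITT ORR is not biased by this.

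**What to change.** Redefine the PP set as treated patients who met the key eligibility criteria and had no major protocol violation. Keep as non-responders those who stop before two cycles or lack a scan because of death, progression (clinical or radiologic) or treatment-related toxicity. Exclude a patient for missing response data only when the reason is unrelated to outcome. Listing the reason for each PP exclusion beside the result would let readers see what separates the two estimates.

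The cost is a sentence or two in the population definition. The PP ORR will probably be slightly less favourable and closer to the ITT ORR. The primary analysis, sample size and patient treatment do not change.
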